##### Aerobic exercise

Aerobic exercise will be based on their current activity levels. The aerobic physical activity information provided will help participants with suggestions for increasing activity and meeting the physical activity guidelines (if appropriate) for those living with and beyond cancer [13, 61–63]. In addition, the information provided (see Fig. 10) will give examples of exercises with a collapsible drop-down option detailing supplementary information regarding aerobic recommendations and considerations covering the FITT (frequency, intensity, time, and type) principle in detail. Aerobic exercise information is provided based on the participants’ current self-reported aerobic exercise. Using the government guidance of 150 moderate–75 vigorous minutes per week, the participants recorded their current level of aerobic activity. ExerciseGuide UK then illustrated how the participant can increase their aerobic activities in smaller bouts of aerobic activity to reach the recommended guidance [13].

**Fig. 10 Fig10:**
[figure not shown]
Example-tailored advice for a participant who self-reported 50 physical activity minutes per week. The pink button will release a collapsible drop-down box detailing considerations for aerobic activity, including the FITT principle

##### Virtual meeting

The participants will meet with one member of the research team at the start of week 1 and week 4 online using video conferencing software or via standard telephone calls. In both meetings, the researcher will walk through the exercise prescription, ascertain the safety of exercises for the participant, and encourage engagement with the programme. The efficacy of behaviour change interventions has been illustrated with human interaction and support, with improvements in adherence and effectiveness of digital interventions [64].

#### Additional intervention components

##### Action planning

ExerciseGuide UK contains a module dedicated to developing an action plan. The action plan within ExerciseGuide UK includes a tunnelled transition following background and introductory information regarding SMART goals. To build the action plan, the website provides examples that help participants think of specific details in relation to being active (e.g. what activity, when, where, how long, and with whom)**.** Upon completion of the questions, the website will offer a structured action plan. The action plan can be modified over the 8 weeks at the user’s discretion and printed off.

Action plans have demonstrated an essential strategy for intended behaviour change by bridging the so-called intention-behaviour gap [65]. Action plans have been included on previous iterations of ExerciseGuide [66] and variations of the computer-tailored platform such as workplace sitting [67, 68]. Furthermore, a systematic review noted that action planning within eHealth interventions has been effective for behaviour change [69].

##### Tracking

An online tracking module has been created to support participants to track their physical activity and general thoughts. The tracking module will provide a mix of open and closed questions regarding aerobic and resistance exercise, health-related fitness, motivation and habits, and general comments. Additionally, the tracking module will provide tailored feedback. This module will be released weekly, though a selection of data (motivation and health status) will be pulled through to subsequent weeks for graphical features (e.g. enablers and health/symptom check-in). Visual aids such as responsive graphs can present past and present data to show progress. The participants will be sent an email reminder upon the release of the tracking module.

##### Extra information

The extra information page acts as a library of cancer-specific information written in layman’s language.

##### Contact form

The website contains an integrated contact form where the participants can email the research team directly. This integrated contact form auto-populations the participant’s name and email for convenience. A copy of the email is sent to the participant’s email they have registered with the platform.

### Measures

#### Feasibility

The feasibility of the study will be assessed via the rate of recruitment and retention over the study duration.

#### Acceptability

The acceptability of ExerciseGuide UK will be assessed using a mixed-methods approach. The participants will be guided into a module with an integrated satisfaction survey upon completing week 8. This survey was modelled of the Systems Usability Scale with questions being tailored to ExerciseGuide. The satisfaction survey was adopted from the Canadian version of ExerciseGuide for those with a diagnosis of breast cancer. In addition, the participants will be provided with the opportunity for real-time module feedback using a five-point Likert scale (1—poor to 5—excellent) and open-ended feedback [70]. Finally, after completing the 8-week programme, 15 participants will be invited to participate in an interview to explore further the satisfaction of the online platform and virtual communication. These will be offered to participants following completion of the study.

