#### Usability

In addition to the satisfaction survey will be the Systems Usability Scale [71]. The Systems Usability Score is a 10-item questionnaire with five responses ranging from “strongly disagree” to “strongly agree” [71]. The final question allows respondents to provide further comments in an open-ended format. The criteria for the System Usability Score is ≥ 68% [71, 72].

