#### Website usage

Engagement will be assessed using ExerciseGuide UK stored database information and Google analytics integrated website tracking software [73]. The number of times a participant has entered a module answered questions, and tracking log will be counted to establish website and module engagement [74]. Furthermore, Google analytics will be used to examine the time spent on specific modules reading feedback or library articles, as well as to assess non-usage attrition (i.e. the process of participants not using ExerciseGuide UK as intended or at all). Participation in pre-, mid-, and post-telehealth sessions will be noted.

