#### Health-related outcomes

Health-related outcomes will be collected at baseline upon registration to the website and immediately following the completion of week 8. The health-related outcomes being assessed pre- and post-study will be the quality of life, anxiety, and depression. Health-related quality of life will be explored via the 30-item European Organisation for Research and Treatment of Cancer Quality of Life Questionnaire-validated questionnaire (EORTC QLQ-C30; version three) [75]. The quality of life domains are divided into multi-item subscales, functional (e.g. physical, role, cognitive, emotional, and social), symptom scales (e.g. fatigue, pain, nausea/vomiting, and dyspnoea), financial hardship, and global health status.

Anxiety and depression will be measured using the Hospital Anxiety Depression Scale [76]. The Hospital Anxiety Depression Scale will measure anxiety and depression using a 14-item scale (seven items for depression and seven items for anxiety). The Hospital Anxiety Depression Scale has been illustrated to show an excellent screening of those with and without clinical symptoms of depression and anxiety to longer questionnaires (MADRS-S and STAI-S) using web-based platforms for those living with and beyond cancer [77].

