##### Qualitative data

Qualitative data will be obtained via two modalities. Firstly, open-ended questions will be provided in the satisfaction survey at the end of week 8 to elicit qualitative feedback. Any qualitative feedback provided will be exported to a single software for thematic analysis. Secondly, following the completion of the programme, 15 interviews will be conducted and will continue if not saturated. Interviews aim to expand on the quantitative satisfaction questions by exploring prior or current barriers to physical activity and the potential impact (e.g. behaviour and attitude change), usability, and friendliness of ExerciseGuide UK.

All interviews will be transcribed verbatim and analysed using thematic analysis. Using inductive coding, transcriptions will be interpreted, and codes will be generated. The strength of convergence of generated themes will be examined based on the overlapping frequency and range.

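### The three pre-set acceptability criteria rest on end-of-programme instruments, so the acceptability verdict is likely to be tilted towards participants who reach the end

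*Protocol article*

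**What the plan says.** The abstract and the Study design section make feasibility and acceptability the primary outcomes. Under Pre-established criteria, acceptability has three tests: a System Usability Score of at least 68%, a positive mean in the end-of-study satisfaction survey (no cut-off given), and positive themes in the follow-up interviews.

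The data for these tests are timed as follows.

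- **Satisfaction survey** (Acceptability): "The participants will be guided into a module with an integrated satisfaction survey upon completing week 8".
- **Interviews** (Acceptability): "after completing the 8-week programme, 15 participants will be invited to participate in an interview". The Qualitative data section agrees: "following the completion of the programme, 15 interviews will be conducted and will continue if not saturated".
- **Usability scale** (Usability): it has no time point of its own and is introduced only as an addition to the survey: "In addition to the satisfaction survey will be the Systems Usability Scale [71" (the quote stops inside a citation).

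The secondary health outcomes follow the same pattern: "Health-related outcomes will be collected at baseline upon registration to the website and immediately following the completion of week 8".

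Two sources do not depend on reaching the end. During the programme, "the participants will be provided with the opportunity for real-time module feedback using a five-point Likert scale", together with open-ended comments. The Website usage section plans to use web analytics "to assess non-usage attrition (i.e. the process of participants not using ExerciseGuide UK as intended or at all". Neither source enters the three acceptability criteria.

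**The concern.** A participant who stops early, whether from illness, difficulty with the site or dislike of it, has no described route into any of the three criteria. The introduction lists breathlessness, fatigue, pain and symptom burden as barriers in this population, so stopping is unlikely to be unrelated to how acceptable the programme is.

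At stake is a primary outcome that informs whether and how a larger study is planned. The Conclusion says the study should reveal usability problems that can be corrected before larger trials. People who stopped because of such problems are the most useful informants, yet the stated triggers make them the least likely to be heard. Usage data can show that they stopped, but not why. Opinions that were never collected cannot be recovered in the analysis.

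**Working it through.** **Step 1. Can an early stopper reach each criterion?**

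| Criterion | Timing in the text | Route for an early stopper |
|---|---|---|
| Usability score ≥ 68% | None stated; accompanies the survey | None described |
| Satisfaction mean | On completing week 8, as a site module | None described |
| Interview themes | After the programme | None described |

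Module feedback and usage data are open to early stoppers but feed no criterion.

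**Step 2. How many can be missing while retention still passes?** From the protocol, N = 35 and the retention criterion is at least 85%. Since 0.85 × 35 = 29.75, 30 participants are needed (30/35 = 85.7%; 29/35 = 82.9% fails). Up to five can be lost. This is only a guide to missing surveys, because retention is defined as completing 80% of the intervention, so a retained participant may still not reach the end-of-programme survey.

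**Step 3. Could the missing scores change the usability verdict?** The protocol gives no expected scores and no sample size calculation, so there is no stated figure to reproduce. The means below are assumptions. Let c be the number of completers, m their mean score, and x the unobserved mean of the rest.

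- Mean over all enrolled = (c·m + (35 − c)·x) / 35
- Tipping point, at which this mean equals 68: x = (68 × 35 − c·m) / (35 − c), where 68 × 35 = 2380

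| c | m | Tipping point x |
|---|---|---|
| 30 | 70 | (2380 − 2100)/5 = 56 |
| 30 | 72 | (2380 − 2160)/5 = 44 |
| 30 | 75 | (2380 − 2250)/5 = 26 |
| 30 | 80 | (2380 − 2400)/5 = −4, not attainable |
| 25 | 75 | (2380 − 1875)/10 = 50.5 |

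For c = 30 and m = 70, the mean over all enrolled for a range of x is:

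- x = 30: (2100 + 150)/35 = 64.3
- x = 40: (2100 + 200)/35 = 65.7
- x = 50: (2100 + 250)/35 = 67.1
- x = 60: (2100 + 300)/35 = 68.6

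The row with 25 completers corresponds to 25/35 = 71%. If completion and retention coincide, the retention criterion has then already failed.

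The satisfaction mean and the interview themes have no numerical threshold, so no equivalent calculation is possible for them.

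**The case against.** The case on the other side has five parts.

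1. **Early stoppers do have a voice.** Module feedback is part of the acceptability assessment. Weekly tracking, the sessions in weeks 1 and 4 and the contact form also allow comments. A reader might infer that people who stop are never asked and that acceptability is judged by finishers alone. The text does not support that. What stands is narrower: none of these sources enters the pre-set criteria.
2. **Completing week 8 may be a calendar event.** Modules are released over time, with a countdown on the dashboard, so a low user could still reach the survey. That is a fair reading, and it weakens the claim for low users. It does not help someone who no longer logs in, because the survey is itself a module on the site.
3. **The timing of the usability scale is inferred.** This is correct, and it matters because this is the only acceptability criterion with a number. Placing it alongside the survey is the natural reading, but Table 1 and Fig. 1, which might settle it, were not available in the text reviewed.
4. **Drop-out is judged separately.** The retention criterion limits losses if the study is called feasible. It is only a partial safeguard: it uses a different definition, and acceptability could be declared met while retention fails.
5. **An article condenses the full protocol.** Withdrawal procedures and missing-data rules may be set out elsewhere, and their absence is not the point made here. The collection triggers, however, are stated in the article itself.

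**Conclusion.** The concern holds for the three acceptability criteria. Followed as written, the stated triggers are likely to tilt a primary outcome towards participants who reach the end of the programme.

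The effect decides the usability verdict mainly when the completers' mean is near 68. With five of 35 missing, a completer mean of 70 is fragile (tipping point 56), a mean of 75 is fairly robust (26), and a mean of 80 cannot be overturned. These figures rest on assumed scores and on the usability scale being given together with the survey.

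Two stronger readings should not be drawn. First, a reader might infer that finishers are those who liked the programme. In this population stopping may equally reflect illness or death, so reaching the end is all that can be said. Second, a reader might infer that the changes in quality of life, anxiety and depression are biased upwards. They have the same timing, but they are secondary and decide no success criterion. The direction of any bias is also not established: fitter participants may have less room to improve.

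This should be corrected, but it does not undermine the study as a whole.

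**What to change.** 1. Offer the usability scale, the satisfaction survey and the week-8 questionnaires to every enrolled participant at calendar week 8, by email or phone if they no longer use the site, and to willing participants at withdrawal. State this time point for the usability scale explicitly.
2. Draw some of the 15 planned interviews from low users and withdrawers who agree.
3. Report each acceptability criterion with the number of respondents out of all enrolled. Break non-response down by reason, keeping illness and death apart from disengagement.
4. Add a tipping-point analysis of the usability score, as in the working above. Giving every non-responder a below-threshold score would be a poor substitute, because it would count illness or death as poor usability.

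The cost is some reminder emails or calls and a changed sampling rule for the interviews. If the total stays at 15, fewer interviews will be with full completers. Some non-completers will decline, so the tilt will be reduced and made visible rather than removed.

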#### Usability

In addition to the satisfaction survey will be the Systems Usability Scale [71]. The Systems Usability Score is a 10-item questionnaire with five responses ranging from “strongly disagree” to “strongly agree” [71]. The final question allows respondents to provide further comments in an open-ended format. The criteria for the System Usability Score is ≥ 68% [71, 72].

#### Website usage

Engagement will be assessed using ExerciseGuide UK stored database information and Google analytics integrated website tracking software [73]. The number of times a participant has entered a module answered questions, and tracking log will be counted to establish website and module engagement [74]. Furthermore, Google analytics will be used to examine the time spent on specific modules reading feedback or library articles, as well as to assess non-usage attrition (i.e. the process of participants not using ExerciseGuide UK as intended or at all). Participation in pre-, mid-, and post-telehealth sessions will be noted.

#### Health-related outcomes

Health-related outcomes will be collected at baseline upon registration to the website and immediately following the completion of week 8. The health-related outcomes being assessed pre- and post-study will be the quality of life, anxiety, and depression. Health-related quality of life will be explored via the 30-item European Organisation for Research and Treatment of Cancer Quality of Life Questionnaire-validated questionnaire (EORTC QLQ-C30; version three) [75]. The quality of life domains are divided into multi-item subscales, functional (e.g. physical, role, cognitive, emotional, and social), symptom scales (e.g. fatigue, pain, nausea/vomiting, and dyspnoea), financial hardship, and global health status.

Anxiety and depression will be measured using the Hospital Anxiety Depression Scale [76]. The Hospital Anxiety Depression Scale will measure anxiety and depression using a 14-item scale (seven items for depression and seven items for anxiety). The Hospital Anxiety Depression Scale has been illustrated to show an excellent screening of those with and without clinical symptoms of depression and anxiety to longer questionnaires (MADRS-S and STAI-S) using web-based platforms for those living with and beyond cancer [77].

#### Data management

ExerciseGuide UK website uses a modern framework (CakePHP) that provides a baseline security level. ExerciseGuide UK runs on a trusted hosting platform only over Hypertext Transfer Protocol Secure (HTTPS), using current Transport Layer Security versions. HTTPS is a secure method of sending data between a web server and a web browser. The passwords are never stored as plain text. They will be stored as a salted encrypted hash.

#### Data analysis

##### Pre-established criteria

The feasibility will be assessed based on the pre-established criteria detailed below:The recruitment target of 35 has been reached within the allocated 5 months.Recruitment rate: ≥ 60%.Recruitment rate will be assessed by the number of eligible patients approached relative to the number of participants enrolling in the study.Retention rate: ≥ 85%Retention rate will be assessed as the number of participants who complete 80% of the intervention over the 8-week duration.

Recruitment and retention rates have been established based on a recent systematic review of online supportive care for those LWBLC [40].

Acceptability will be assessed based on the following pre-established criteria:System Usability Score ≥ 68% [71, 72]Positive participant satisfaction illustrated in the end of study survey presented as a mean value on a scalePositive themes identified in follow-up interviews

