### Participants and screening

The participants will be recruited through the lung cancer clinic at Hull University Teaching Hospital. The primary investigator will disseminate the recruitment information with assistance from participating site oncologists to those who meet the inclusion criteria during routine appointments. Interested participants will contact a member of the research team to obtain informed consent, provide answers to any outstanding questions, and process baseline data collection. Figure 1 illustrates a flow diagram of participant engagement.

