### Eligibility

The participants will be screened against predetermined eligibility criteria and approved for physical activity by their clinician. The participants must have received a lung cancer diagnosis or cancer of the lung (e.g. pleural mesothelioma), either non-small cell lung cancer or small cell lung cancer. In addition, the participants must be 18 years or older, able to speak and communicate in English, be willing to provide informed consent, have access to a smart device that can display the website (e.g. laptop or tablet), and have internet access.

The participants will be considered ineligible if they are under 18 years of age at the time of screening, unable to provide informed consent due to cognitive or linguistic inability, or have a physiological and/or cognitive impairment that would prevent or inhibit participation of moderate aerobic and resistance-related physical activity. In addition, the participants will be excluded if they have identified bone metastases in weight-bearing locations and/or spinal compression, which may inhibit or prevent their safe participation in unsupervised exercise.

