##### Sample size

Given that this study is a feasibility study with pre-established criteria for success instead of a primary outcome assessment, a formal sample size calculation is not necessary [46]. The sample size for this study is a maximum of 35 individuals LWBLC. The sample size was based on the previous research into online supportive care for those LWBLC and clinician expertise. Firstly, previous research exploring online supportive care for those LWBLC was considered. A recent review reported a mean sample size of eight studies examining online supportive care for those LWBLC [40]. Of the eight studies, six were pilot and feasibility studies. The mean sample size over the six pilot and feasibility studies was 29 ± 33, which demonstrated satisfactory detection of feasibility and acceptability concerns. Furthermore, literature highlighted 35 participants is satisfactory per group [78]. Secondly, clinical expertise was sought out. Based on the recommendation from a senior academic lung cancer clinician based on the studies specified recruitment period (5 months) based on multiple considerations (e.g. caseload and eligibility criteria). Furthermore, the sample of 35 individuals consulted with statistician regarding to ensure adequate size to determine feasibility issues.

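### The ≥60% recruitment-rate criterion is written with its ratio inverted (approached ÷ enrolled), so as worded it cannot detect poor uptake

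*Protocol article*

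**What the plan says.** The Pre-established criteria section of the protocol article gives three feasibility criteria. The first is a volume target: "The recruitment target of 35 has been reached within the allocated 5 months". The second is a rate, "Recruitment rate: ≥ 60" per cent, with this definition: "the number of eligible patients approached relative to the number of participants enrolling in the study". The third is a retention rate of at least 85%. No other part of the article gives the recruitment ratio the other way round.

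Two other sections bear on who counts as an eligible patient approached. The Eligibility section says participants must "be willing to provide informed consent, have access to a smart device that can display the website", along with having internet access. Under Participants and screening, recruitment information goes "to those who meet the inclusion criteria during routine appointments", and then "Interested participants will contact a member of the research team to obtain informed consent".

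The Sample size section says that "a formal sample size calculation is not necessary", on the ground that success is judged by pre-established criteria.

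**The concern.** A recruitment rate should fall when fewer of the patients approached agree to join. The definition puts the larger count first, so the quantity moves the opposite way and a lower limit of 60% cannot catch a problem.

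This matters because the criteria carry the study's main conclusion. The abstract says the primary outcome is assessed against pre-established feasibility criteria, and the Feasibility section under Measures names only recruitment and retention. The article also says that it is published partly to set out its pre-determined criteria and to aid replication. A reader who applies this one literally would pass any level of uptake.

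There is a smaller, related point. Once the ratio is the right way up, its denominator is eligible patients approached. Because willingness to consent is an inclusion criterion, someone could argue that a patient who declined was never eligible. The article does not say how such patients are counted.

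**Working it through.** **Inputs.** From the article: threshold 60%; target and maximum sample 35; the definition of the rate. The article gives no number of patients approached, so every such number below is an assumption. Write A for eligible patients approached and E for participants enrolled. Recruitment is through the clinic where patients are approached, so E ≤ A.

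**The plan's own figure.** The 60% is a threshold and not a calculated result, and 35 has no formal calculation behind it, so there is nothing to reproduce. The check is on how the ratio behaves.

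**Step 1: the ratio as written, A/E.** Since A ≥ E, A/E ≥ 1 whenever anyone enrols (with none enrolled it is undefined). Enumerating every pair with E ≤ A for A from 1 to 300 gives a minimum of 1.0. To fall below 60% with E = 35, A would have to be below 0.60 × 35 = 21, fewer than the number enrolled, which is impossible.

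**Step 2: both ratios at E = 35.**

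| Approached (assumed) | As written, A/35 | Turned round, 35/A |
|---|---|---|
| 35 | 100.0% | 100.0% |
| 58 | 165.7% | 60.3% |
| 59 | 168.6% | 59.3% |
| 100 | 285.7% | 35.0% |
| 200 | 571.4% | 17.5% |

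Every row meets 60% in the middle column, and the figure rises as uptake gets worse. In the last column the bar separates good from poor uptake.

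**Step 3: where the corrected bar falls.** 35/A ≥ 0.60 requires A ≤ 35/0.60 = 58.3, so at most 58 approached.

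**Step 4: does the handling of decliners matter after correction?** Assume A = 100 and E = 35, leaving 65 who did not enrol. Let R of them be reclassified as not eligible because they were unwilling. The rate is 35/(100 − R):

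- R = 0: 35/100 = 35.0%, fails
- R = 40: 35/60 = 58.3%, fails
- R = 55: 35/45 = 77.8%, passes
- R = 65: 35/35 = 100%, passes

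The result crosses 60% at R = 42, because 100 − 42 = 58. So the treatment of decliners can change the verdict, but it does not make failure impossible.

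**The case against.** The strongest reply is that this is loose prose and not a formula. Both counts are named, a 60% floor makes sense only for enrolled ÷ approached, and no analyst is likely to report a recruitment rate of 286% as a success. As to intent, that stands. It does not rescue the text: the sentence is the only definition of the criterion in the article, it is given in full, and it is wrong. This is not detail left to a fuller document.

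A second reply is that the criterion of 35 participants in 5 months can still be failed. That also stands and limits the consequence, although that criterion measures volume and not uptake among those approached.

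A reader might go further and infer that the eligibility wording makes the bar impossible to fail even after the ratio is turned over. The documents do not support that. Under Participants and screening, information goes to people already taken to meet the inclusion criteria, and the decision to make contact and consent comes afterwards. On that sequence decliners naturally stay in the denominator. The related exclusion concerns inability to consent for cognitive or linguistic reasons, not refusal. Step 4 shows that failure remains possible even if many refusers are removed. What survives is an ambiguity worth closing.

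Nor should the device and internet requirements be read as hiding a barrier. They are legitimate entry conditions for a web-based tool, and the Discussion discloses access openly, listing it first among its limitations without calling it the main one.

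**Conclusion.** The recruitment-rate criterion is inverted. As worded it is at least 100% whenever anyone enrols, rises as uptake falls, and so cannot signal poor recruitment. This rests only on the enrolled being a subset of the approached. The size in any example depends on an assumed number approached: at 35 enrolled and 100 approached, 286% as written against a true uptake of 35%.

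The failure to discriminate comes from the inversion alone. The listing of willingness to consent as an inclusion criterion is a secondary ambiguity about the denominator. One of three feasibility criteria is affected, the intended meaning is readily recovered, and the accrual target still works. It should nevertheless be corrected, because it is a decision rule for the primary outcome.

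**What to change.** Replace the definition with: recruitment rate = participants enrolled ÷ eligible patients approached. Add that patients who were approached and then declined, or never made contact, remain in the denominator, and that willingness to consent is not used to remove them. Settle this before the rate is calculated.

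The threshold can stay at 60%. The change costs one or two sentences and uses the two counts the criterion already names. The downside is that the reported rate may be less favourable: with the full 35 enrolled, the criterion is missed as soon as 59 eligible patients have been approached.
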